## Abstract

**Background:**

Although most births in Mali occur in health facilities, a substantial number of newborns still die during delivery and within the first 7 days of life, mainly because of existing training deficiencies and the challenges of maintaining intrapartum and postpartum care skills.

**Objective:**

This trial aims to assess the effectiveness and cost-effectiveness of an intervention combining clinical audits and low-dose, high-frequency (LDHF) in-service training of health care providers and community health workers to reduce perinatal mortality.

**Methods:**

The study is a three-arm cluster randomized controlled trial in the Koulikoro region in Mali. The units of randomization are each of 84 primary care facilities. Each trial arm will include 28 facilities. The facilities in the first intervention arm will receive support in implementing mortality and morbidity audits, followed by one-day LDHF training biweekly, for 6 months. The health workers in the second intervention arm (28 facilities) will receive a refresher course in maternal neonatal and child health (MNCH) for 10 days in a classroom setting, in addition to mortality and morbidity audits and LDHF hands-on training for 6 months. The control arm, also with 28 facilities, will consist solely of the standard MNCH refresher training delivered in a classroom setting. The main outcomes are perinatal deaths in the intervention arms compared with those in the control arm. A final sample of approximately 600 deliveries per cluster was expected for a total of 30,000 newborns over 14 months. Data sources included both routine health records and follow-up household surveys of all women who recently gave birth in the study facility 7 days postdelivery. Data collection tools will capture perinatal deaths, complications, and adverse events, as well as the status of the newborn during the perinatal period. A full economic evaluation will be conducted to determine the incremental cost-effectiveness of each of the case-based focused LDHF hands-on training strategies in comparison to MNCH refresher training in a classroom setting.

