### Sample Size

A sample size of 600 births per cluster was calculated to have 80% power to detect a reduction in the perinatal mortality rate from 30% to 27% live births, which corresponds to a 10% reduction in the perinatal mortality rate between intervention and control arms (α=5%, intracluster correlation of 0.003, and coefficient of variation of cluster size 0.9 and a 0.96 correlation of baseline measures with outcome). The number of clusters available per arm was 28. The expected average number of deliveries per month in each cluster was approximately 38, resulting in 16 months of follow-up. Two additional months of data collection are planned to account for losses and refusals and allow for adjustments in the analysis, resulting in a final average cluster size of approximately 675 births over 18 months.

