## Results

The trial is completed. The recruitment began on July 15, 2019, and data collection began on July 23, 2019, and was completed in November 2020. Data cleaning or analyses began at the time of submission of the protocol. As the randomization is performed at the health facility level, we will undertake aggregate cluster-level analysis comparing the proportion between treatment arms [30]. We will compare differences in the proportion of perinatal mortality between intervention and control groups using a chi-square statistic adjusted for the effect of clustering within health facilities [31] using a formula that incorporates the intraclass correlation coefficient as a measure of the extent of clustering [32].

The analysis and report of the intervention effect will be carried out in accordance with CONSORT (Consolidated Standards of Reporting Trials) principles and its extension for pragmatic trials [33].

We will perform all analyses using Stata version 16.1 software (Stata Corp).

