### Strengths of the Study

The distinctive feature of this intervention compared with the other LDHF interventions is that it adopts problem-based learning, including supervision and audits with feedback [14]. Thus, the audit component will identify knowledge gaps related to the maternal and neonatal care provided in the facilities and then identify the appropriate training modalities to correct deficiencies in the management of maternal and neonatal care around the delivery and in the postpartum period.

The analytical approaches will provide evidence about the benefits and costs of this pragmatic intervention to improve the quality of maternal and newborn care in Mali with the aim of reducing perinatal mortality. The results will provide policy makers and practitioners with crucial information to facilitate the translation of best practices in capacity strengthening for health care providers in the routine practice of maternal and child care services. Indeed, although LDHF hands-on training has been implemented and evaluated in some resource-limited settings with the aim of reducing maternal and perinatal mortality, previous studies have analyzed only a few outcomes [17,21].

Another distinctive feature of this trial is that it adopts a pragmatic and holistic approach, and the analysis will contain both qualitative and quantitative data collected over a period of 14 months. The trial will provide a better understanding of how LDHF hands-on training of health care providers and community health workers could complement routine care to improve maternal and child health outcomes in resource-limited settings. In addition, this trial occurs during routine health service delivery and will demonstrate the potential of routinely collecting health management information system data to analyze the effectiveness of a major public health intervention.

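### The abstract's 30,000 newborns over 14 months contradicts the design of 84 clusters of about 600 births, which gives 50,400, and the 16 and 18 months in Sample Size

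*Protocol article*

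**What the plan says.** The abstract (Methods) describes three arms of 28 facilities: "The units of randomization are each of 84 primary care facilities". It then gives size and duration in one sentence: "A final sample of approximately 600 deliveries per cluster was expected for a total of 30,000 newborns over 14 months".

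The Sample Size section of the main text says "A sample size of 600 births per cluster was calculated to have 80% power" and "The number of clusters available per arm was 28". It expects about 38 deliveries per cluster per month and so 16 months of follow-up. It adds two months for losses and refusals, "resulting in a final average cluster size of approximately 675 births over 18 months".

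Strengths of the Study returns to the shorter period, describing "both qualitative and quantitative data collected over a period of 14 months". The Results section reports that recruitment began on 15 July 2019 and that "data collection began on July 23, 2019, and was completed in November 2020".

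**The concern.** The abstract's sentence does not multiply out, and its duration disagrees with the section that derives the sample size. A gap of 20,400 newborns is too large for rounding, and because the 14 months appears twice it is not a single slip in the abstract.

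The planned size is the benchmark for judging whether the trial reached its target. A trial that ended with 40,000 births, say, would look oversized against 30,000, short against 50,400 and shorter still against 56,700. Many readers will see only the abstract.

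**Working it through.** **Inputs.** Clusters: 84, 28 per arm (abstract; Sample Size). Births per cluster: 600 as the power target, about 675 with the loss allowance (Sample Size). Deliveries per cluster per month: about 38 (Sample Size). Abstract total and duration: 30,000 over 14 months. Data collection: 23 July 2019 to November 2020 (Results). The end day is not given, so 1 to 30 November is used as a range.

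**1. Does Sample Size agree with itself?** Yes.
- 600 / 38 = 15.8, about 16 months; 38 × 16 = 608.
- 38 × 18 = 684, close to 675 (600 × 18/16 = 675 exactly).

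**2. The total.**
- 84 × 600 = 50,400. The stated 30,000 is (50,400 − 30,000) / 50,400 = 40% lower.
- 84 × 675 = 56,700 with the allowance.
- 30,000 / 84 = 357 births per cluster. Over 14 months that is 25.5 a month, not 38.

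**3. The duration.**
- 38 × 14 = 532 births per cluster, not 600. Over 84 clusters that is 44,688, which is also not 30,000.

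**4. The dates.**
- 23 July 2019 to 1 November 2020 is 467 days; to 30 November, 496 days. Divided by 30.4375 these are 15.3 and 16.3 months.
- Counting from the start of recruitment (15 July) gives 475 to 504 days, or 15.6 to 16.6 months.
- Against 18 months the shortfall is between 1.4 and 2.7 months, whichever start date and November day are used.

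**5. Power at each size.** Assumptions: rates of 30 and 27 per 1000, two-sided 5%, ICC 0.003, CV 0.9, r = 0.96, and a baseline correction applied to the whole design effect. This reading reproduces the plan's stated 80%.

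DE = [1 + ((1 + CV²)m − 1) × ICC] × (1 − r²)

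At m = 600: [1 + (1.81 × 600 − 1) × 0.003] × (1 − 0.9216) = 4.255 × 0.0784 = 0.334. The effective number per arm is 28 × 600 / 0.3336, about 50,360. The standard error of the difference is √[(0.03 × 0.97 + 0.027 × 0.973) / 50,360] = 0.00105. Then 0.003 / 0.00105 − 1.96 is about 0.90, and power is 81.6%, in line with the plan.

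| Births per cluster | DE | Power |
|---|---|---|
| 357 (30,000 / 84) | 0.230 | 75.7% |
| 532 (14 months) | 0.305 | 80.5% |
| 600 (16 months) | 0.334 | 81.6% |
| 675 (18 months) | 0.366 | 82.6% |

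**The case against.** The best defence is that the derivation itself is sound. Sample Size is one consistent chain in which 600 is the power target and 675 is that target plus an allowance. The 80% power attaches to the 600 that the abstract repeats. This stands: the document does not hold several competing power calculations, and only the 30,000 and the 14 months are out of line.

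The second defence concerns the dates. A reader might infer that the two-month allowance was not delivered and that 675 per cluster was not reached. The documents do not support that. The 18 months is a plan and the dates report conduct. Facility records are collected retrospectively and verbal autopsies wait 40 days, so the data-collection period need not equal the period over which births accrued. The article gives neither the accrual period nor an achieved count, and 38 a month is only an expectation. What remains is that data collection lasted less than the planned 18 months and that the article does not say so.

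Third, a reader might suppose that 30,000 counts only two arms, because 56 × 38 × 14 = 29,792. That needs 532 births per cluster, whereas the sentence says 600, and 56 × 600 = 33,600. Fifty clusters of 600 would give exactly 30,000. The text supports none of these origins.

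Finally, the power figures depend on a reading of the effect size. The article prints a "reduction in the perinatal mortality rate from 30% to 27% live births". Taken literally, those percentages give essentially 100% power at 357, 532 and 600 per cluster under the same formula.

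**Conclusion.** The point holds for the total and the duration, and needs nothing beyond the article's own numbers. The abstract's 30,000 is 40% below the 50,400 implied by its own clusters and births per cluster. Its 14 months supports about 532 births per cluster rather than 600, and conflicts with the 16 and 18 months in Sample Size. The reported data-collection period is 1.4 to 2.7 months shorter than the planned 18, without comment.

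It would be wrong to conclude that 600 per cluster is an error or that power collapses. Under the assumptions stated, power is still about 80% at 532 per cluster and falls to about 76% at 357. Those figures rest on rates per 1000 and on the assumed 0.96 correlation acting on the whole design effect. Neither the arithmetic of the total nor that of the duration depends on them.

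**What to change.** In the abstract and in Strengths of the Study, replace the 30,000 and the 14 months with figures that agree with Sample Size: 50,400 newborns over 16 months as the power target, and about 56,700 over 18 months with the loss allowance. In Results, state that data collection was shorter than the planned 18 months and, if known, give the period over which births accrued.

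If 30,000 is the real expected or achieved total, or covers only some clusters, say which and restate power at that size with the rates in their correct unit.

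The cost is a few sentences. Design and analysis do not change, and a power calculation has to be restated only if 30,000 stands.

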**Results:**

The trial is complete. The recruitment began on July 15, 2019, and data collection began on July 23, 2019, and was completed in November 2020. Data cleaning or analyses began at the time of submission of the protocol.

**Conclusions:**

The results will provide policy makers and practitioners with crucial information on the impact of different health care provider training modalities on maternal and newborn health outcomes and how to successfully implement these strategies in resource-limited settings.

**Trial Registration:**

ClinicalTrials.gov NCT03656237; https://clinicaltrials.gov/ct2/show/NCT03656237

**International Registered Report Identifier (IRRID):**

DERR1-10.2196/28644

## Introduction

### Background

Mothers and their babies are at the highest risk of death during delivery and during the first week postpartum [1]. Even though 59% of births in sub-Saharan African countries now occur in health facilities [2], in 2018, approximately 2.476 million babies died during the first 28 days of life, with approximately 1 million dying during the first day of life and almost another 1 million within the first week [3,4]. In Mali, an estimated 67 stillbirths [5] and an additional 75 newborn deaths [6] occur on average every day; the predominant causes are birth asphyxia, prematurity, and sepsis [7]. The maternal mortality ratio in Mali is 562 per 100,000 live births [3], almost 2.7-fold the global rate [3]. Most of these deaths are because of factors related to the place of delivery and quality of care [4,8]. In particular, the lack of appropriately trained staff in facilities, delays in referrals, and inadequate supplies and equipment are evident in many resource-poor settings [9]. This suggests that high-quality care, especially during late pregnancy, childbirth, and the early newborn period, are essential [10], and simple evidence-based interventions are likely to meaningfully reduce the number of maternal deaths, stillbirths, and early neonatal deaths [11,12].

Traditional capacity-building models for training health care providers, delivered through off-site classroom-style lectures or directed reading, are still the norm in low- and middle-income countries [8,13,14]. However, to disrupt the delivery of services, these approaches have been found to have limited (if any) impact on learning outcomes, and any knowledge and skills gained are neither transferred to other coworkers at the facility nor translated into improved provider practice and performance [13,15]. Moreover, there is no evidence that these methods contribute to knowledge retention after training, and limited conclusions can be drawn about their long-term impact on measures of performance in terms of service quality and maternal and newborn outcomes. A review of intervention studies aimed at improving the performance of health workers in low- and middle-income countries has suggested that problem-based learning and competence-based learning [15], including supervision and audits with feedback [13,14], along with brief team learning sessions within the workplace (health facility), using simulation, followed by simulation-based practice and feedback, can improve learning outcomes and provider performance compared with training approaches that do not include subsequent practice [13,16].

Over the last few years, an increasing number of African countries have implemented competency-based training of health care providers with the goal of improving maternal and child health outcomes and reducing perinatal mortality [17-19]. Low-dose, high-frequency (LDHF) training is a type of competency-based training that promotes maximal retention of clinical knowledge, skills, and attitudes through short, targeted, simulation-based learning activities, delivered during several in-service sessions and reinforced with structured practice sessions [20].

In that vein, in response to a World Health Organization report on health systems and policy indicators documenting that Mali did not have a policy on maternal, perinatal, and neonatal death audit (World Health Organization 2014), Mali’s Ministry of Public Health and Hygiene made it mandatory to report maternal, perinatal, and neonatal deaths and adverse events within 48 hours of their occurrence, through the Integrated Disease Surveillance and Response Network, and to convene an audit of the events within 15 days of the notification.

Mali’s national directive to implement facility-based maternal and perinatal morbidity and mortality audits offers an opportunity to leverage it and target training on skills and competency gaps identified during audits. However, to the best of our knowledge, the potential of using facility-based maternal and perinatal morbidity and mortality audits to identify areas that require attention for subsequent LDHF hands-on training has not yet been exploited. Moreover, even though LDHF hands-on training has demonstrated a significant positive impact on maternal and early neonatal outcomes, including reduced rates of fresh stillbirth and first-day mortality [17,21], retained placenta, and postpartum hemorrhage [19]. Limited conclusions can be drawn about the impact of LDHF hands-on training on maternal and neonatal care practices during intrapartum and postpartum periods and other perinatal outcomes, especially 7-day mortality and morbidity. There is very little known about the cost-effectiveness and the processes of implementation of LDHF training [22,23].

### Objective

This study proposes a strategy to leverage maternal and perinatal morbidity and mortality audits being implemented in Mali, as a basis for identifying gap areas that can be addressed by a case-based focused LDHF on-site training strategy within primary health care–level facilities (Centre de Santé Communautaire [CSCOM]). These trainings will also target community-based causes of mortality and morbidity in health facilities. The trial will assess the effectiveness of LDHF hands-on training informed by maternal and neonatal mortality audits in reducing perinatal mortality and in increasing adoption of key maternal and newborn care practices during the delivery and the postpartum period. Secondary objectives include assessment of the implementation process and the cost-effectiveness of the intervention.

## Methods

### Study Setting

The study will be conducted in 4 districts in the Koulikoro region, Mali. The study area was selected as it is part of a larger project implemented by the Canadian Red Cross in collaboration with the Malian Red Cross (Croix-Rouge Malienne). This project is an integrated 4-year (2016-2020) maternal neonatal and child health (MNCH) intervention that targets 6 districts across the Koulikoro and Sikasso regions and is funded by the Government of Canada. The project supports the primary and secondary health facilities (CSCOMs and Centre de Santé de Référence [CSREF]—referral health centers) to improve the quality of their MNCH services and strengthen the health management information system. At the community level, the Malian Red Cross has a strong presence because of the training and support of local community health workers and volunteers for MNCH-related activities at remote integrated management of childhood illness sites.

The Koulikoro region is the second-most-western region of Mali. It covers an area of 90,120 square kilometers. With an estimated population in 2017 of 3.1 million and a density of 26.8 people per square kilometer. The Koulikoro region is separated into 7 districts: Kati, Kangaba, Koulikoro, Kolokani, Nara, Banamba, and Dioïla. The Canadian Red Cross and Malian Red Cross program encompasses the latter five. Of these, 4 districts (Koulikoro, Kolokani, Banamba, and Dioïla) will be included in this study.

### Trial Design

This pragmatic (effectiveness) cluster randomized controlled trial will be implemented in 84 community health facilities (CSCOM) in the Koulikoro region, Mali. Facilities will be randomly allocated into either of two intervention arms or the control arm.

Intervention arm 1: audit and feedback with LDHF hands-on training and 6 months follow-up.Intervention arm 2: MNCH refresher training and audit, and feedback with LDHF hands-on training and 6 months follow-up.Control arm: allocated to receive MNCH refresher training and follow-up.

### Cluster Size and Selection

Community health facilities, including community health workers serving the catchment area, are the units of randomization (clusters). Although there are some differences in the services provided at these facilities according to the baseline facility assessment conducted in December 2016, only those health facilities providing basic obstetric care with at least one health care provider trained in the active management of the third stage of labor (AMTSL), essential newborn care (ENC), perinatal care (PNC), and those who had not yet started implementing the audits are considered for inclusion in the study. All facility deliveries (both mother and newborn) within study clusters and live home births referred to a facility within the perinatal period are included in the trial, subject to informed consent. In that respect, a master list of 84 facilities meeting the inclusion criteria within the 4 districts will be generated.

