#### Consent to Participate

Written consent will be obtained from mothers or fathers of newborns at the follow-up household visit and for verbal autopsy. If the mother is not able to give consent, her husband or other adult family member will be requested to give consent to participate in the study. If the respondent cannot read, the consent statement will be read to them, and a thumb impression by the respondent in place of a signature will signify consent. The data collector will explain the risks and benefits to potential enrollees before conducting the verbal autopsy and administering the household questionnaire in the intervention and control clusters. Participants will be informed that they have the right to withdraw from the study at any time and that there are no penalties from doing this, and this will not in any way affect their ability to receive any health care services.

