### Primary Outcome

The perinatal mortality rate per 1000 live births occurring in each facility and the corresponding catchment area for the births that had taken place in the facility will be used to assess the effectiveness of the intervention. It is defined as the sum of *fetal deaths* (stillbirth), defined as the death of a fetus weighing 500 g or more, or of 22 weeks of gestation or more, occurring in health facilities, and *early neonatal death*, namely, the death of a live born within the first 7 days of life occurring in the facility or in the community. As health facility studies are not an appropriate source of data for calculating perinatal mortality incidence [24] unless all babies are born and stayed in a health facility for 7 days, the data on perinatal mortality will be extracted from both facility-level data and household survey questionnaires.

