### Data Collection Methods

#### Health Facility Data

All the facilities in the intervention and control clusters will be visited once a month to retrospectively and systematically collect detailed data from partographs and registries for all facility births and any newborn that was not delivered in the facility but was referred to the facility for PNC within the first 7 days following birth.

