#### Household-Level Interviews

The data collectors will also conduct a follow-up home visit (during the monthly health facility data collection visit, described above) to all women who recently gave birth in facilities since their last visit to administer a short questionnaire after at least 7 days postpartum to capture any perinatal death, complications, or adverse events, the status of the newborn during the perinatal period, and the mother’s satisfaction with the health care during the facility delivery.

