#### Verbal Autopsy in the Household

In the case of perinatal death in the household recorded during their monthly visits, the data collector will pay a visit after the 40-day bereavement period to conduct a verbal autopsy. Two local independent physicians will review each completed verbal autopsy and assign the cause of death using International Classification of Diseases 10th Revision. If the two physicians do not assign the same diagnosis, a third physician (adjudicator) will review the two causes of death and assign a final cause of death.

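### Facility births are included only subject to consent, but the only family consent described comes after the 7-day outcome is fixed; the condition should cover household data only

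*Protocol article*

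**What the plan says.** Under Cluster Size and Selection, the protocol article says that all facility deliveries in the study clusters, and live home births referred to a facility in the perinatal period, "are included in the trial, subject to informed consent".

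Under Consent to Participate, the only family consent described is this: "Written consent will be obtained from mothers or fathers of newborns at the follow-up household visit and for verbal autopsy". The same section adds: "The data collector will explain the risks and benefits to potential enrollees before conducting the verbal autopsy and administering the household questionnaire". It also allows proxy consent: "If the mother is not able to give consent, her husband or other adult family member will be requested to give consent".

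The timing is given elsewhere. Under Household-Level Interviews, collectors visit "to administer a short questionnaire after at least 7 days postpartum to capture any perinatal death, complications, or adverse events". Under Verbal Autopsy in the Household, "the data collector will pay a visit after the 40-day bereavement period to conduct a verbal autopsy".

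Under Primary Outcome, the endpoint is stillbirth in a health facility plus early neonatal death, that is "the death of a live born within the first 7 days of life occurring in the facility or in the community". It is drawn from both facility data and household questionnaires. Under Health Facility Data, monthly visits are to "collect detailed data from partographs and registries for all facility births", with no mention of consent.

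**The concern.** The inclusion clause attaches consent to membership of the trial, not just to the interview. Consent is sought only after the outcome window has closed and the family knows the result. Read literally, the clause selects births after randomisation and after the outcome.

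The deaths at stake are facility stillbirths and early deaths already in the register whose families then refuse. If bereaved families refuse more often than others, the measured mortality rate falls. If refusal among bereaved families also differs between arms, the comparison itself is distorted. The planned effect is only a 10% relative reduction, so a modest difference would matter. The extra two months of data collection allowed for losses do not help, because a larger sample does not remove selection.

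**Working it through.** **1. Order of events**

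| Step | When | Section |
|---|---|---|
| Outcome occurs | Birth to day 7 | Primary Outcome |
| Register extraction, all facility births | Monthly, retrospective | Health Facility Data |
| Household consent and questionnaire | Day 7 or later | Consent to Participate; Household-Level Interviews |
| Verbal autopsy consent | After 40 days | Consent to Participate; Verbal Autopsy in the Household |

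No consent step precedes the outcome.

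**2. The plan's own figure and the target effect**

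The Sample Size section gives 600 births per cluster, 28 clusters per arm, ICC 0.003, cluster-size CV 0.9, baseline correlation 0.96 and 80% power. It prints the rates as percentages. I read them as 30 and 27 per 1000, which reproduces the stated power, and assume a two-sided 5% test.

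- Design effect = 1 + [(1 + 0.9²) × 600 − 1] × 0.003 = 4.255.
- Effective n per arm = 28 × 600 / [4.255 × (1 − 0.96²)] = 16,800 / (4.255 × 0.0784) ≈ 50,400.
- An individually randomised comparison needs 48,292 per arm for 80% power. Power here is 81.6%, so the stated figure reproduces.
- Expected deaths per arm are 16,800 × 0.030 = 504 and 16,800 × 0.027 ≈ 454. The target is about 50 deaths.
- Moving from 600 to 675 births per cluster raises power only to 82.6% and leaves any selection bias as it was.

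**3. Effect of outcome-dependent consent**

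The protocol gives no consent rates, so those below are assumptions. With true rate p, consent c_d among bereaved families and c_a among others:

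observed rate = p·c_d / [p·c_d + (1 − p)·c_a], with p = 0.03 and c_a = 0.95.

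- c_d = 0.95: 30.0 per 1000.
- c_d = 0.90: 0.0270 / 0.9485 = 28.5 per 1000 (5% low).
- c_d = 0.85: 0.0255 / 0.9470 = 26.9 per 1000.
- c_d = 0.80: 0.0240 / 0.9455 = 25.4 per 1000 (15% low).

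*Unequal refusal, no true effect:* 85% in one arm and 95% in the other gives 26.9 / 30.0 = 0.898.

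*Gap that imitates a 10% reduction, 5% of survivors lost:* control-arm loss of deaths of 5%, 10% or 20% requires intervention-arm loss of 14.8%, 19.3% or 28.2%, a gap of 8 to 10 points.

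*Equal refusal, true 10% reduction:* with c_d = 0.80 in both arms, the 27 per 1000 arm is observed at 0.0216 / 0.94595 = 22.8 per 1000. The ratio is 22.8 / 25.4 = 0.90, so the comparison is essentially intact.

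**4. If only register-recorded deaths are affected**

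Let these be a share s of all deaths (not given), and let the 10-point gap act on them alone, so that c_d = 0.95 − 0.10s in the affected arm.

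- s = 0.50: c_d = 0.90, ratio 28.5 / 30.0 = 0.95.
- s = 0.75: c_d = 0.875, rate 0.02625 / 0.94775 = 27.7 per 1000, ratio 0.92.
- s = 1: ratio 0.90.

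**The case against.** The strongest reply is that nothing in the protocol says register deaths are removed. Health Facility Data covers all facility births without a consent condition. Primary Outcome uses both sources. Limitations of the Study plans to triangulate facility and household deaths so as to reduce underreporting. Consent to Participate ties consent to the household visit and verbal autopsy. Together these support a reading in which register deaths stay in. That stands: a reader might infer that the trial deletes them, and the document does not support it as fact. But this reading conflicts with the wording of the inclusion clause, and no section says which prevails.

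A reader might also infer that families who have moved or cannot be found are excluded. The clause speaks of consent only and is silent on non-contact.

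A difference between arms is speculative. Collectors are independent of intervention delivery and follow one consent procedure in all clusters, and audit cases are anonymised. Proxy consent and home visits aided by community volunteers reduce loss. Collectors are not blinded, so a difference is possible, but nothing points to a 10-point gap.

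Finally, an article may leave the analysis set to a fuller document. That excuses missing detail, but here an inclusion rule is stated and sits badly with the data collection described.

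**Conclusion.** The point holds as a conflict between a stated inclusion rule and the rest of the protocol. Taken literally, the rule permits selection after the outcome and would lower the measured perinatal mortality rate if bereaved families refuse more often.

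Its effect on the treatment comparison is conditional. A gap of roughly 8 to 10 percentage points between arms in loss of deaths would imitate the whole planned effect. Equal loss would leave the rate ratio at about 0.90 when the truth is 0.90. The 5% and 15% shortfalls therefore concern the level of the rate, and should not be read as bias in the comparison.

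These sizes rest on assumed consent rates, a true rate of 30 per 1000, and loss acting on all perinatal deaths. If only part of the deaths are register-recorded, the share that the clause puts at risk is smaller (section 4 of the working). Deaths at home after discharge depend on the household interview under either reading.

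**What to change.** Reconcile Cluster Size and Selection, Consent to Participate and Health Facility Data:

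- Limit the consent condition to the household questionnaire and verbal autopsy.
- State that register-recorded births, stillbirths and facility deaths in randomised facilities enter the primary analysis regardless of household consent or contact, once it is confirmed that the ethics approvals cover such use of register data.
- Treat babies discharged alive without household follow-up as having unknown day-7 status, not as survivors. Counting them as survivors would bias the rate downward, and the Primary Outcome section itself warns against facility data alone unless babies stay 7 days. Add a sensitivity analysis over plausible mortality in this group.
- Report refusal and non-contact by arm and by outcome in the register.

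The cost is an ethics confirmation, a sentence or two of text and a little extra analysis. Register data were already planned for all facility births, so no new collection is needed, and the change can be made at the analysis stage although recruitment is over. Home deaths in families never contacted remain unrecoverable.
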